##### **2.2 Secondary**

###### ***Infant***

**SI1:** To compare antibody responses to pertussis antigens (concentration of IgG antibody to PT, pertactin (PRN), filamentous haemagglutinin (FHA) and fimbrial antigens 2 and 3 (FIM 2 and 3)), tetanus toxoid, diphtheria toxoid and polio serotypes 1, 2 and 3 at birth amongst infants born to mothers who received REPEVAX in pregnancy compared to infants whose mothers received BOOSTRIX-IPV in pregnancy

**SI2:** To compare antibody responses to pertussis antigens [IgG to PT, PRN, FHA and FIM 2 and 3], Hib antigen [PRP], tetanus toxoid, diphtheria toxoid and polio serotypes 1, 2 and 3; meningococcal serogroup C serum bactericidal antibody titres and meningococcal serogroup C-specific IgG concentrations; 13 serotype-specific pneumococcal IgG concentrations and functional pneumococcal antibody studies at 2, 5 and 13 months of age (just before and one month after primary immunization and one month after booster vaccines) in infants born to mothers who received REPEVAX in pregnancy compared to infants whose mothers received BOOSTRIX-IPV in pregnancy and compared to infants whose mothers who did not receive pertussis vaccination in pregnancy

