### ***Mother***

**SM1:** To determine concentrations of antibodies to pertussis antigens [IgG to PT, PRN, FHA and FIM 2 and 3] and tetanus toxoid, diphtheria toxoid and polio serotypes 1, 2 and 3, in pregnant women prior to administration of the REPEVAX or BOOSTRIX-IPV vaccine and at the time of delivery

**SM2:** To estimate the placental transfer ratio of antibodies to pertussis antigens [IgG to PT, PRN, FHA and FIM 2 and 3] and tetanus toxoid, diphtheria toxoid and polio serotypes 1, 2 and 3, in mothers who received REPEVAX in pregnancy compared to mothers who received BOOSTRIX-IPV in pregnancy

**SM3:** To compare concentrations of antibodies to pertussis antigens [IgG to PT, PRN, FHA and FIM 2 and 3] and polio serotypes 1, 2 and 3 at 12-13 months post-delivery in women who received REPEVAX or BOOSTRIX-IPV vaccine and to those women who did not receive pertussis vaccination in pregnancy

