## **3. Design**

Full details are in the study protocol. Briefly women will be recruited at two sites during routine antenatal appointments and randomised to receive either REPEVAX or BOOSTRIX in pregnancy. A separate group of women who did not receive vaccination in pregnancy will be recruited at post natal visits as a control group.

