### **3.2 Randomisation and blinding**

Randomisation is from a block randomisation list produced prior to the study. On recruitment to the study, each subject will be allocated, in order of inclusion, the next available subject number. The study number will define the group to which the mother is assigned and which pertussis-containing vaccine she will receive. Mothers and their infants who are recruited in the postnatal period as part of the control group will not be randomised. Laboratory staff that test maternal and infant blood samples for vaccine responses will be blinded to the group allocation. Pregnant women and other study personnel will not be blinded. Though written informed consent will be taken at the first visit, continued consent to participate will be ascertained at each subsequent visit.

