### **10.4 Immunogenicity analysis**

The end points in PE,SI1,SI2,SM1,SM2,SM3 are either concentrations, titres, ratios of concentrations or titres or binary values(for being over a threshold). For concentrations and titres (and ratios of these) results will be log transformed and the groups (REPEVAX vs BOOSTRIX-IPV, OR REPEVAX vs BOOSTRIX-IPV vs Control) compared by normal errors regression (equivalent to ANOVA for 3 groups or an unpaired t-test for 2 groups). Geometric means for each group will be calculated with 95% confidence intervals and Geometric mean fold ratios between groups with 95% CIs. If the log transformed data are not normally distributed then the kruskal-wallis test will be used to compare the groups.

Proportions above titre thresholds will be compared using Fisher's exact test and proportions calculated within groups with 95% exact confidence intervals.

For persistence (SM3) geometric mean fold changes will be calculated with 95% CI.

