### **10.5. Additional exploratory analyses**

In regression analyses of titres the effect of titre pre vaccination (at 2m) on post primary responses (at 5m and also 13m to the same and different antigens) will be assessed. Regression models to allow for timing of the blood after primary vaccination (or birth), sex, ethnicity, gestational age at vaccination (or weeks prior to birth), study site, gestational age and birth weight will be fitted to investigate these factors and adjust if necessary.

Prior receipt of pertussis vaccination in pregnancy will be investigated for the pre-vaccination maternal blood.

The association between antibodies at birth in infants and at 2 months will be investigated.

The association between breast feeding and post primary responses.

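### The comparisons with unvaccinated controls (SI2, SM3) are not randomised, yet their main analysis is group-only and adjustment is left to an exploratory, undefined option

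*SAP*

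**What the plan says.** Section 3 describes the controls as a group apart: "A separate group of women who did not receive vaccination in pregnancy will be recruited at post natal visits as a control group". The vaccinated women are recruited at antenatal appointments. Section 3.2 is explicit on allocation: "Mothers and their infants who are recruited in the postnatal period as part of the control group will not be randomised".

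Two secondary objectives in section 2.2 use this group. SI2 sets infant antibody at 2, 5 and 13 months in the vaccine arms "compared to infants whose mothers who did not receive pertussis vaccination in pregnancy". SM3 compares maternal antibody at 12 to 13 months after delivery in the vaccine arms with levels in the unvaccinated women ("to those women who did not receive pertussis vaccination in pregnancy").

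Section 10.4 states the analysis for all end points together. Log concentrations and titres have "the groups (REPEVAX vs BOOSTRIX-IPV, OR REPEVAX vs BOOSTRIX-IPV vs Control) compared by normal errors regression", described as "equivalent to ANOVA for 3 groups or an unpaired t-test for 2 groups". The fallback is also group-only: "If the log transformed data are not normally distributed then the kruskal-wallis test will be used to compare the groups". Threshold proportions go to Fisher's exact test.

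Section 10.5, headed as exploratory, lists models on timing of blood, sex, ethnicity, gestational age at vaccination (or weeks from vaccination to birth), study site, gestational age and birth weight, which "will be fitted to investigate these factors and adjust if necessary".

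**The concern.** Randomisation justifies a group-only test of REPEVAX against BOOSTRIX-IPV. Nothing comparable supports the same test of either vaccine against Control. Women who were not vaccinated in pregnancy and joined after delivery may differ from trial recruits in age, ethnicity, site and other respects that bear on antibody levels. Section 10.4 does not separate the two kinds of contrast, so both would be reported with the same kind of confidence interval and p-value, although for the control contrasts neither allows for confounding.

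These contrasts are the trial's only information on maternal vaccination against none, for pertussis, Hib, tetanus, diphtheria, polio and pneumococcal responses. (Section 5 drops the meningococcal outcomes for the control group.) If adjustment stays optional with no stated criterion, the choice between crude and adjusted estimates can be made after both are known.

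**Working it through.** **1. What the main model contains.** A regression equivalent to ANOVA or an unpaired t-test has group as its only term. Kruskal-Wallis and Fisher's test, as specified, also use group alone. So no main analysis of SI2 or SM3 carries a covariate.

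**2. What section 10.5 adds.**

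| Item | Usable for vaccine vs Control? |
|---|---|
| Timing of blood, sex, ethnicity, site, gestational age, birth weight | Yes, defined in all infant groups |
| Gestational age at vaccination, or weeks from vaccination to birth | No, undefined for unvaccinated mothers |
| Maternal age | Tabulated in 10.3, absent from the 10.5 list |
| Criterion for adjusting | None given |
| Link to SI2 or SM3 control contrasts | None given |
| Threshold end points | Not covered; the models are for titres |

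**3. The SAP's own figures.** Section 4 gives log10 SDs of 0.28 (PT), 0.76 (Hib), 0.50 (MenC SBA) and 0.37 (tetanus), and detectable folds of 1.38, 2.37, 1.77 and 1.52 with 65 per arm. Power is not stated; I take 80% and a two-sided 5% level. Detectable fold = 10^[SD × √(2/65) × (1.96 + 0.84)] gives 1.37, 2.36, 1.76 and 1.52, so the SDs and sample size are consistent. These figures concern the randomised contrast only.

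**4. Illustration of confounding.** The SAP gives no covariate effects or imbalances, so these are assumptions. Suppose there is no true vaccine effect and one factor multiplies antibody by a fold f, with prevalence differing between groups by d.

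- Bias (log10) = d × log10(f).
- SE = SD × √(1/65 + 1/30) = SD × 0.2207.
- Rejection rate = Φ(−1.96 + bias/SE) + Φ(−1.96 − bias/SE).

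Scenario A: f = 1.3, d = 0.30. Bias = 0.30 × 0.1139 = 0.034, a 1.08-fold shift. 
Scenario B: f = 1.5, d = 0.50. Bias = 0.50 × 0.1761 = 0.088, a 1.22-fold shift.

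| Antigen | SD | SE | Scenario A | Scenario B |
|---|---|---|---|---|
| PT | 0.28 | 0.0618 | 8.6% | 29.7% |
| Tetanus | 0.37 | 0.0817 | 7.0% | 19.0% |
| Hib | 0.76 | 0.1677 | 5.5% | 8.2% |

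If the 18 infants from the Infanrix Hexa study are pooled (section 5), there are 48 controls and the PT rates become 9.8% and 37.9%. More controls shrink the standard error but not the bias. The pooling check compares controls with controls, so it says nothing about vaccinated against unvaccinated mothers.

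**5. Can thresholds be adjusted too?** At the 95% response level used in section 4, 65 + 65 + 30 = 160 infants give about 160 × 0.05 = 8 non-responders, and 30 controls about 1.5. A logistic model with two group terms and six or more covariates could fail to converge or separate.

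**The case against.** The strongest reply is that adjustment is already planned. Section 10.5 names most of the covariates one would want. The SAP is also open about the controls not being randomised, the primary end point excludes them, both infant groups share the same routine schedule and blood-sampling windows from 2 months on (section 3.1), and the laboratory is blinded. These features limit differences in timing and measurement between the groups recruited in this trial.

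Much of this stands, and it rules out several stronger readings. A reader might infer that the plan has no adjustment, or that it passes the controls off as randomised; neither is so. A reader might take 30% as the expected error rate. It needs a 1.5-fold factor, a 50-point imbalance and the smallest SD in section 4 all together; under the same scenario Hib gives 8%. A reader might also want Fisher's test replaced throughout, but with so few expected non-responders it is a defensible choice.

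What the reply does not answer is the status of the adjustment. Shared schedules and blinding do not remove confounding by who was vaccinated, and an exploratory model used at discretion leaves the crude result as the stated secondary analysis.

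**Conclusion.** The point holds in a limited form. For the vaccine-against-Control contrasts in SI2 and SM3, the stated main analysis is group-only although the groups are not randomised. The covariate models in 10.5 are exploratory, conditional without a criterion, not tied to these contrasts, and include terms that controls cannot have. The plan followed as written would give headline estimates open to confounding, with intervals that ignore it.

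The size and direction of the bias cannot be determined from the SAP. The rejection rates above show only that moderate imbalance could matter, more for PT than for Hib; they rest on assumed effects and imbalances, 65 against 30, and one confounder acting alone.

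A reader might infer that the trial's main result is at risk. It is not: REPEVAX against BOOSTRIX-IPV, including the primary end point, is validly analysed unadjusted.

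**What to change.** In section 10.4, separate the two kinds of contrast.

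- **REPEVAX vs BOOSTRIX-IPV:** keep the unadjusted analysis as the randomised comparison.
- **Each vaccine vs Control, concentrations and titres:** make the headline the log-scale regression with a fixed covariate set defined in all groups, fitted whether or not the covariates are significant. For infants (SI2): timing or age at blood sample, sex, ethnicity, study site, gestational age at birth and birth weight (from 10.5), plus maternal age (from 10.3). For mothers (SM3): maternal age, ethnicity, site and time from delivery to sample. Show the crude ratio alongside and label these contrasts observational.
- **Thresholds:** keep Fisher's exact test and label the control comparison crude.
- **External infants:** if the 18 are pooled, give the adjusted estimate with and without them. Leave out of the pooled model any covariate they lack or that is collinear with study source; the SAP does not say which sites or covariates are available for them.

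The cost is SAP wording, one further model per end point, a few degrees of freedom out of about 160 infants, and the loss of infants with a missing covariate. Confounding by unmeasured factors would remain, which is why the label is needed as well as the model.

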#### **4. Sample Size**

Based on sample size calculations below, it is proposed that a convenience sample of 65 (+/-10) mother-infant pairs will be recruited into each of the two groups that received a pertussis vaccine in pregnancy, with a control group of 30 (+/-10) women and their infants. Up to 200 mother-infant pairs will be recruited to take account of mother-infant pairs lost to follow-up.

The sample size calculation is based on data from the recent P13UK study performed by PHE. Based on these results, the standard deviation of the post-primary vaccination GMCs (log-10 scale) was: PT = 0.28, Hib = 0.76, MenC SBA = 0.50, Tet = 0.37. Based on these SD with 65 per study arm fold differences of 1.38, 2.37, 1.77 and 1.52 would be detectable between the vaccine arms for PT, Hib, MenC and Tet respectively. In terms of percentages reaching putative protective levels 95% in one arm would be different to percentages below 77% in the other arm. The protocol has more details on other sample sizes.

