### **10.2 Significance level and confidence intervals**

95% confidence intervals will be reported. Where comparisons are made between groups a 5% significance level will be used.

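### For SI2 and SM3, a non-randomised control group shares one unadjusted, equal-variance model with the two randomised arms

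*SAP*

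**What the plan says.** **Who the controls are.** SAP section 3.2 states: "Mothers and their infants who are recruited in the postnatal period as part of the control group will not be randomised". Section 4 plans 30 of them, give or take 10. Section 5 may add 18 infants from another study if a comparison with the recruited controls shows no difference at p < 0.005.

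**Where they enter.** Under section 6.2, only SI2 (infants at 2, 5 and 13 months) and SM3 (mothers at 13 months) cover all groups. Section 5 withdraws the meningococcal outcomes for controls. The primary end point (6.1) and SI1, SM1 and SM2 concern vaccinated mothers or their infants only.

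**How they are analysed.** Section 10.4 has the groups on the log scale "compared by normal errors regression (equivalent to ANOVA for 3 groups or an unpaired t-test for 2 groups", with group as the only term. It asks for geometric mean ratios between groups with confidence intervals, and falls back on a Kruskal-Wallis test if the logs are not normal. It has no unequal-variance option. It does not say whether the REPEVAX versus BOOSTRIX-IPV ratio in a three-group end point comes from the three-group model or from the two arms alone.

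**Adjustment.** Section 10.5, headed as exploratory, lists blood timing, sex, ethnicity, site, gestational age, birth weight and "gestational age at vaccination (or weeks prior to birth". Models with these factors "will be fitted to investigate these factors and adjust if necessary". No trigger for adjusting is given.

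**The concern.** Two kinds of comparison share one model. REPEVAX versus BOOSTRIX-IPV is protected by randomisation. Vaccinated versus unvaccinated is observational: the groups were recruited at different times and by different routes, and some infant controls may come from another study. Three things follow.

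- The main estimate of a stated secondary comparison is unadjusted, and the choice whether to adjust is left until the data can be seen.
- One residual SD serves all groups. If the control SD differs, the intervals for the control contrasts have the wrong width. So does the randomised interval, if it is read from the same fit.
- A three-group global test can be significant because of the controls alone. It does not tell the reader whether the two vaccines differ, and when the Kruskal-Wallis fallback applies it is the only test named.

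The adjustment list also needs care. Timing of vaccination in pregnancy does not exist for unvaccinated mothers, so a model with that term cannot include them.

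**Working it through.** **1. Inputs.** Section 10.2: "Where comparisons are made between groups a 5% significance level will be used"; two-sided testing is assumed. Section 4 gives log10 SDs "PT = 0.28, Hib = 0.76, MenC SBA = 0.50, Tet = 0.37" and says "with 65 per study arm fold differences of 1.38, 2.37, 1.77 and 1.52 would be detectable". Power is not stated; 80% is assumed. No control SD is given, so control/arm SD ratios r from 0.5 to 2 are assumed.

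**2. The plan's own figure.** Detectable fold = 10^[(1.960 + 0.842) × SD × √(2/65)]. For PT: 2.802 × 0.28 × 0.1754 = 0.1376, and 10^0.1376 = 1.37. The four values are 1.373, 2.363, 1.761 and 1.520; with the noncentral t they are 1.376, 2.379, 1.768 and 1.525. They agree with the plan to within rounding. At 90% power they would be 1.44, 2.71, 1.92 and 1.62, which do not match, so 80% is a fair reading. These figures concern the two randomised arms only.

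**3. What pooling does to the SD.** With arms of 65 and n controls, the pooled SD relative to the arm SD is about

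w = √{[128 + (n − 1)r²] / (127 + n)}.

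For n = 30: r = 0.5 gives √(135.25/157) = 0.928, and r = 2 gives √(244/157) = 1.247.

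**4. Error rates.** A simulation of 400,000 replicates per scenario, with arm SD 0.28 and 30 controls, gave the following. Error rates are 100% minus coverage, for nominal 5%.

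| r | w | error, arm vs control | error, REPEVAX vs BOOSTRIX-IPV | power for 1.38-fold PT between arms |
|---|---|---|---|---|
| 0.5 | 0.928 | 1.0% | 6.9% | 0.845 |
| 0.75 | 0.959 | 2.5% | 6.0% | 0.829 |
| 1 | 1.000 | 5.0% | 5.0% | 0.808 |
| 1.25 | 1.051 | 8.0% | 4.0% | 0.778 |
| 1.5 | 1.109 | 10.9% | 3.0% | 0.744 |
| 2 | 1.247 | 16.2% | 1.5% | 0.650 |

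The last two columns apply only if the randomised interval is taken from the three-group fit.

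Check at r = 2. The true SE of arm versus control is SD × √(1/65 + 4/30) = 0.386 SD. The model uses 1.247 × √(1/65 + 1/30) = 0.275 SD. The model SE is too small by a factor of 1.40, which gives a two-sided error near 16%.

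The number of controls also matters. At r = 1.5 and r = 2 the control-contrast error is 13.0% and 20.2% with 20 controls, and 9.5% and 13.1% with 40.

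**5. Confounding.** Its size cannot be derived from the SAP. To show sensitivity, take SD 0.28, 65 versus 30, and no true effect. Then SE = 0.28 × √(1/65 + 1/30) = 0.0618. Assumed log10 biases of 0.05, 0.10 and 0.15 (1.12-, 1.26- and 1.41-fold) give false-positive rates of about 13%, 37% and 68%. These are illustrations, not estimates for this trial.

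**The case against.** The strongest reply is that section 10.4 already lists REPEVAX versus BOOSTRIX-IPV as a comparison in its own right and plans pairwise ratios, so nothing obliges the analyst to use the three-group SD or to rest conclusions on the global test. That stands as far as it goes: the SAP leaves the matter open rather than deciding it wrongly. But it does not separate the two contrasts where all groups are analysed, and the rank-test fallback yields no pairwise result.

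Four stronger readings are tempting, and the SAP does not support them.

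- **The randomised comparison is certainly distorted.** This needs both an unequal control variance and an interval taken from the three-group fit. The SAP establishes neither. At SD ratios from 0.75 to 1.25 with 30 controls, the error rate moves by about one point, and the point estimate is unbiased throughout.
- **Controls sit almost all at the assay floor.** Near-constant controls would raise the randomised error rate to about 7.6% with 30 controls and 9.4% with 48. The case with 48 is implausible: the 18 external infants have no 2-month blood, so they can join only at 5 and 13 months, after vaccination, and they add no mothers to SM3. A control group piled up at one censored value should also trigger the rank test, although ratio intervals could still be affected.
- **Adjustment would drop every control.** Section 10.5 speaks of several models and does not prescribe one three-group fit containing timing of vaccination. The term must be left out of control contrasts; the SAP does not show that it would be kept.
- **The control contrasts are shown to be confounded.** Non-random recruitment makes confounding a risk. Section 10.5 does list several relevant covariates, but only as exploratory and without a rule.

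**Conclusion.** The point holds for SI2, other than meningococcal outcomes, and for SM3. The main vaccine-versus-control analysis is unadjusted, although the controls are not randomised, and it assumes equal variances with no alternative. This is the firmer part. The confounding cannot be sized from the SAP. The miscalibration with 30 controls is about 11% to 16% at SD ratios 1.5 to 2 and about 1% at 0.5, with no distortion if the SDs are equal.

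The effect on REPEVAX versus BOOSTRIX-IPV is conditional and smaller: about 7%, 5% and 1.5% at ratios 0.5, 1 and 2, and only if the three-group model supplies the interval.

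A reader might infer that the trial's main result is at risk. It is not: the primary end point, SI1, SM1 and SM2 compare the two randomised arms only. The figures rest on two-sided 5% testing, 65 per arm, 30 controls and assumed control SD ratios. The matter is worth correcting because the remedy is cheap and removes a choice that would otherwise be made after seeing the data.

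**What to change.** Amend section 10.4 as follows.

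- **Randomised contrast.** Estimate REPEVAX versus BOOSTRIX-IPV from the two randomised arms only, at every time point, including when the rank test is used. Its interval then no longer depends on the control SD. If the arms share a variance, coverage is 95% and power for a 1.38-fold PT difference is about 0.81.
- **Control contrasts.** Report each arm against control separately, labelled observational, with unequal-variance or robust standard errors. Make a prespecified adjustment the main control analysis, using covariates defined in all groups. For infants: site, sex, ethnicity, gestational age at birth, birth weight and blood timing. Blood timing should be age at the 2-month sample, when no primary dose has yet been given, and days since the last dose at 5 and 13 months. For mothers: site, ethnicity, age and sampling time. Leave out gestational age at vaccination and weeks from vaccination to birth.
- **External infants.** The SAP does not show that these covariates exist for the 18. Where one is unavailable, also report the contrast without them.
- **Global test.** Do not base conclusions about the two vaccines on the three-group test.

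The cost is a few lines of SAP text and extra model lines in Stata, a few degrees of freedom, and slightly wider intervals in the control contrasts. Most of the covariates are already named in sections 10.3 and 10.5.

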### 6.1 Primary end point

**PE:** Fold change in PT from blood taken at 2 to 5 months (post primary vaccination) in infants of vaccinated mothers.

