### 6.2 Secondary end points

**SI1:** In the infant at birth (just vaccinated mothers group) - PT, PRN, FHA, FIM2, FIM3, TT (TT0.10/TT1.00) ,Dip (Dip0.10/Dip1.00).

**SI2:** In infants at 2,5 and 13 months (all groups) PT, PRN, FHA , FIM2, FIM3, Hib (Hib0.15, Hib1.00), TT (TT0.10/TT1.00) ,Dip (Dip0.10/Dip1.00), SBA (SBA8, SBA128), MenC, Polio1, Polio2, Polio3 (PolioX\_8), Pn\_x, Pn\_fun\_x.

**SM1:** In Mothers pre vaccination and at delivery (just vaccinated mothers group) - PT, PRN, FHA, FIM2, FIM3, TT (TT0.10/TT1.00) ,Dip (Dip0.10/Dip1.00).

**SM2:** In Mothers/Babies (cord blood) at delivery (just vaccinated mothers group) ratio of Baby to Mother PT, PRN, FHA, FIM2, FIM3, TT (TT0.10/TT1.00) ,Dip (Dip0.10/Dip1.00).

**SM3:** In Mothers (all groups) at 13 months: PT, PRN, FHA, FIM2, FIM3. (And for vaccinated mothers ratio with levels at delivery).

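### The two-arm comparisons do not adjust for the mothers' pre-vaccination antibody level, which probably costs precision at delivery and at birth; any cost on the primary is uncertain

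*SAP*

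**What the plan says.** **Main analysis.** SAP 10.4 covers all the immunogenicity end points (PE, SI1, SI2, SM1, SM2, SM3). After log transformation the arms are compared by a regression that, with two arms, is the same as "an unpaired t-test for 2 groups". No covariate is named.

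**Baseline sample.** The schedule in 3.1 places blood MA at V1, the visit at which the study vaccine is given, for vaccinated mothers. Objective SM1 (2.2) puts the sample before the vaccine. End point SM1 in 6.2 ("In Mothers pre vaccination and at delivery (just vaccinated mothers group")) lists PT, PRN, FHA, FIM2, FIM3, tetanus and diphtheria. Unvaccinated mothers have only blood MC, at 13 months.

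**End points concerned.** The primary (6.1) is "Fold change in PT from blood taken at 2 to 5 months (post primary vaccination) in infants of vaccinated mothers". SI1 is measured "In the infant at birth (just vaccinated mothers group").

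**Planned adjustment.** The exploratory section 10.5 looks at "the effect of titre pre vaccination (at 2m) on post primary responses". It also plans models with birth weight, gestational age at birth and a further set of factors: "timing of the blood after primary vaccination (or birth), sex, ethnicity, gestational age at vaccination (or weeks prior to birth), study site". According to the same section these models "will be fitted to investigate these factors and adjust if necessary". MA is not in that list. 10.5 mentions it only as something to relate to earlier pertussis vaccination in pregnancy.

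**The concern.** MA is measured before the randomised vaccine, so the vaccine cannot have altered it. It is also the same antibody, in the same woman, as the delivery outcome, and antibody in the newborn comes from the mother. Such a covariate usually explains part of the outcome variance. If it is left out, the intervals for the arm comparison are wider than they need be, and a chance difference in starting levels between arms of about 65 stays in the estimate.

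The adjustment in 10.5 does not replace it. It is exploratory, has no criterion for when adjustment is needed, and omits MA. Several of its covariates (the infant's 2-month titre, birth weight, gestational age at birth) arise after the mother is vaccinated. The only antibody level it names as a predictor is that 2-month titre, which the maternal vaccine may itself change.

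**Working it through.** **Inputs.**
- 65 per arm; log10 SDs of post-primary concentrations PT 0.28, Hib 0.76, MenC SBA 0.50, tetanus 0.37; stated detectable folds 1.38, 2.37, 1.77, 1.52 (all SAP section 4).
- 5% significance level (10.2), taken as two-sided.
- 80% power: an assumption, as the SAP states none.
- rho, the within-arm correlation of log MA with the log outcome: not given, so a range is used.

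**Step 1: the plan's own figures.** Detectable fold = 10^[(1.960 + 0.842) × SD × √(2/65)]. For PT: 2.802 × 0.28 × 0.1754 = 0.1376, and 10^0.1376 = 1.373 (1.376 with the t distribution). Hib, MenC and tetanus give 2.363, 1.761 and 1.520 (t: 2.379, 1.768, 1.525). These agree with the stated folds to within about 0.01. The sample size is therefore that of an unadjusted two-arm comparison, consistent with 10.4.

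**Step 2: effect of adding log MA.** Residual variance is multiplied by 1 − rho², interval width on the log scale by √(1 − rho²), and the equivalent unadjusted size is 65/(1 − rho²).

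| Assumed rho | Variance reduction | Interval width multiplied by | Equivalent n per arm |
|---|---|---|---|
| 0.2 | 4% | 0.98 | 65/0.96 ≈ 68 |
| 0.3 | 9% | 0.95 | 65/0.91 ≈ 71 |
| 0.5 | 25% | 0.87 | 65/0.75 ≈ 87 |
| 0.7 | 49% | 0.71 | 65/0.51 ≈ 127 |

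The price is one residual degree of freedom: 127 instead of 2 × 65 − 2 = 128. These multipliers need no SD, so they apply to any of the end points once rho is known.

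**Step 3: where in the table each end point may lie.**
- *SM1 at delivery:* same woman, same antibody. A useful rho is plausible, though the vaccine given in between may weaken it.
- *SI1 at birth:* maternally derived antibody, so again plausible.
- *PE:* a change within the infant from 2 to 5 months. MA can enter through the 2-month denominator, which is plausibly mostly maternal antibody, and through any effect of that antibody on the infant's response. The link is indirect, and rho could be 0.2 or less, where the gain is at most 4%.

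**Step 4: where adjustment is possible.** Hib, SBA, MenC and the pneumococcal outcomes in SI2 have no same-antigen MA value. Polio is in objective SM1 but not in the SM1 end point list. Controls have no MA at all.

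**The case against.** The strongest reply is that nothing here is an error. With randomised arms the unpaired comparison is unbiased, its intervals are valid, and it matches the sample size calculation. That stands: the point concerns efficiency and prespecification.

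It can also be said that the SM1 objective is worded descriptively. But 10.4 includes SM1 among the end points on which groups are compared, so a delivery contrast will be produced.

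A reader might infer three stronger things that the SAP does not support:

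- *That precision is demonstrably lost on the primary.* No correlation is given, and PE is a within-infant change with only an indirect link to MA. Some loss is plausible but not shown.
- *That the detectable PT ratio would fall from 1.38 to, say, 1.32 at rho 0.5.* That figure uses the SD of 0.28, which belongs to the 5-month PT concentration. No SD is given for the fold change, the birth level or the delivery level, so the ratio cannot be carried over to them.
- *That the main arm comparison will be adjusted for the infant's 2-month titre.* 10.4 does not do this; 10.5 examines that titre only as an exploratory question.

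The limits in step 4 also stand. MA adjustment cannot cover all of SI2 or the contrasts with controls, and filling in a missing MA value would conflict with the no-imputation rule in 7.2 unless an exception is written.

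**Conclusion.** The point holds as an efficiency weakness. The main two-arm analyses omit a baseline antibody level that is already scheduled and assayed. The loss is most plausible for SM1 at delivery and SI1; for the primary it is uncertain and may be negligible. Its size runs from 4% of variance at rho 0.2 to 49% at rho 0.7. These correlations are assumptions, and the calculation further assumes a linear relation on the log scale, a common slope in both arms and nearly complete MA data. The validity of the planned test is not in question. The change is still worth making because the covariate costs almost nothing, and naming it in advance is firmer than discretionary adjustment under 10.5.

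**What to change.** In 10.4, for the two randomised arms only and for PT, PRN, FHA, FIM2, FIM3, tetanus and diphtheria:

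- **SM1 (delivery) and SI1:** main analysis by regression of the log outcome on arm plus log MA of the same antigen.
- **PE and same-antigen infant levels at 2 and 5 months:** the same model as a prespecified adjusted analysis.
- **Throughout:** report the unadjusted comparison alongside, and keep the three-group comparisons with controls unadjusted for MA.

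In 7.2, add a stated exception for a missing baseline MA covariate, for example substitution of the overall mean across both arms or a missing indicator. Either is acceptable for a value that precedes the randomised vaccine; outcomes stay unimputed.

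The cost is one degree of freedom per model and a few lines in 10.4 and 7.2. No new samples or assays are needed. The text should be settled before data reach the statistician, as 1.3 requires of the final plan.
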